## Abstract

**Background:**

Perioperative malnutrition is common in patients undergoing gastrointestinal-oncology surgery and is associated with longer hospital stays, increased postoperative complications, poorer quality of life, and lower survival rates. Current practice emphasizes the role of early perioperative nutrition therapy as an early intervention to combat the postoperative complications of patients and the implementation is now widely adopted. However, there is still a lack of research on determining the effectiveness of intensive nutrition therapy and providing ONS perioperative locally. This becomes the significance of this study and serves as a basis for management and guideline in the local hospital settings.

**Methods:**

This is a pragmatic randomized control trial study where elective admitted patients will be randomly divided into the intervention (SS) or control (NN) group. All data will be collected during a face-to-face interview, anthropometric measurement, blood sampling (albumin, white blood count, hemoglobin, and c-reactive protein), handgrip strength, and postoperative complications. Group SS will be receiving a tailored lifestyle and intensively supplemented with oral nutrition support as compared to Group NN that will receive standard medical care. The primary outcome *for this study is* the length of stay in the hospital. Additional outcome measures are changes in biochemical profile and nutritional and functional status. The effects of intervention between groups on the outcome parameters will be analyzed by using the SPSS General Linear Model (GLM) for the repeated measure procedure.

**Discussion:**

The intervention implemented in this study will serve as baseline data in providing appropriate nutritional management in patients undergoing gastrointestinal and oncological surgery.

**Trial registration:**

ClinicalTrials.gov Protocol Registration and Results System (PRS) NCT04347772. Registered on 20 November 2019.

## Background

Recently, the definition of malnutrition, as proposed by the International Global Initiative on Malnutrition (GLIM), refers to a patient’s clinical condition that has at least one (1) phenotypical (involuntary weight loss, low body mass index, reduced muscle mass) or etiological criteria (reduced food intake or assimilation, inflammation, or disease burden) [1]. The levels of malnutrition severity are divided into Stage 1 (Moderate malnutrition) and Stage 2 (Severe malnutrition). This level can be determined by having one (1) phenotypic criterion that meets the grade [1].

Malnutrition is well reported in surgery patients [2, 3] especially those who have undergone major surgery [4–6], and particularly at risk in patients undergoing surgery for upper gastrointestinal or colorectal cancer [7, 8]. Preoperative malnutrition shows an increased length of hospital stay, a higher rate of surgical site infection and mortality [9], and is associated with higher postoperative complications, increased costs, poorer quality of life, and lower survival rates [9, 10]. Studies show a high prevalence of malnutrition or high nutritional risk during hospital admission [11, 12] but this is rarely assessed in the clinical setting, especially for patients who will undergo elective surgery.

The nutrition requirement for surgery is higher in comparison with the normal requirement to support a speedy recovery. Suboptimal nutritional intake will cause further depletion of the patient’s nutritional status preoperatively and a higher risk of postoperative complications. Interestingly, one of the Malaysian studies shows a significant number of post-surgery complications compared to pre-surgery which was associated with a poor level of nutrition [10].

Nutrition therapy is the provision of nutrition or nutrients either orally (regular diet, therapeutic diet, e.g., fortified food, oral nutritional supplements) or via enteral nutrition (EN) or parenteral nutrition (PN) to prevent or treat malnutrition [13] which includes dietary counseling. Nutritional therapy is important as it affects mainly the perioperative maintenance of the nutritional state to prevent postoperative complications [14]. It is strongly recommended not to wait until severe disease-related malnutrition has developed, but to start nutrition therapy early, as soon as a nutritional risk becomes apparent [15].

In addition, for patients with severe nutritional risk in surgical patients with oral feeding, some improvements were shown, resulting in shortened duration of hospital stay and flatus, and some wound and infectious complications [16]. Current practice emphasizes the role of early nutrition therapy as an early intervention to combat the postoperative complications of patients and the implementation is now widely adopted. However, there is minimal local data to present the effects of perioperative nutrition therapy and the process of nutrition management, from screening/assessment on admission to nutritional support and monitoring for surgical patients. Therefore, there is a need for a study in this area to find good practices that should be mandated in routine patient care regardless of disease type, specifically in a local hospital setting.

### Primary objective

The primary objective is to determine the effect of intensive perioperative nutrition therapy on *length of hospital stay* in adult patients undergoing major elective gastrointestinal and oncological surgery over an extended period before hospital admission, during the hospital stay, and after discharge in comparison to a control group of the same type of patients who will receive the standard care.

## Methods/design

### Design

This study will be a single-blinded, pragmatic randomized clinical trial with two arms comparing an intervention group with a control group involving sixty-eight adult patients undergoing major elective gastrointestinal and oncological surgery in Hospital Serdang (HSD).

A pragmatic trial is a randomized controlled trial whose purpose is to inform decisions and the benefit of treatment in clinical practice [17]. Critical aspects of pragmatic trials are that they are conducted in the standard practice setting, they include typical participants to whom the intervention will be applied in practice, the intervention is flexible as it would be in practice, and a range of directly relevant outcomes are assessed [17, 18]. Pragmatic trials indicate the success or failure of realistic interventions in a clinical setting [19]. The RCT conformed to the Consolidated Standards of Reporting Trials (CONSORT) statement for reporting RCT with two arms comparing an intervention group with a control group [20]. After consenting to participate, subjects will be allocated into intervention (SS) and control (NN) groups randomly. The flow diagram for recruitment and randomization is shown in Fig. 1. A graphical presentation of the proposed study procedure and timeline is shown in Fig. 2. The schedule of enrolment, interventions, and assessments are in Table 1 [21].

**Fig. 1 Fig1:**
[figure not shown]
Flow diagram

**Fig. 2 Fig2:**
[figure not shown]
A graphical presentation of the protocol and timeline of the intervention study. Ax: assessment; Hx: history; PG-SGA: Patient-Generated Subjective Global Assessment; ONS: oral nutrition support; LOS: length of stay; SS: intervention group; NN: control group

**Table 1 Tab1:**
[figure not shown]
The schedule of enrolment, interventions, and assessments

*−t*_*1*_*:* Outpatient appointment day

*t*_*1*_*:* First day of hospital admission for planned surgery

*t*_*2*_*:* First day of tolerating solid food in the ward

*t*_*3*_*:* 1 day before discharge from hospital

*t*_*x*_*:* 4 weeks after discharge from hospital

### Study population

Men and women who plan for surgical procedures will be invited to participate in this study with informed consent. A screening form will be used to exclude those who do not meet the inclusion criteria. The inclusion criteria are those who are receiving elective major surgery treatments for gastrointestinal and oncology-related surgery, aged from 18 to 65 years old, Malaysian, able to communicate verbally, Malnutrition Screening Tool (MST) score ≥ 2, and provided and signed informed consent. The exclusion criteria are those who are receiving elective major surgery treatments other than gastrointestinal and oncology-related including bariatric surgery, those who have received preoperative enteral or PN, those who require emergency surgery, complicated with chronic diseases and fluid retention (renal/ cardiovascular/pulmonary/ hepatic), and those who have participated in other research studies.

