### Randomization

An online platform of randomization method will be used to prevent risk allocation concealment. The permuted block randomization will be performed using the following platform, i.e., https://www.sealedenvelope.com [22]. The randomization will be based on a block method for a block size of four, with A for the intervention group and B for the control group. This block of four has six different possible arrangements of two As and Bs. The randomization with body mass index (BMI) and gender stratification will be conducted to assign participants to either Group SS: intervention group or Group NN: control group. The flow diagram for recruitment and randomization is shown in Fig. 1.

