### Statistical analysis

#### Sample size calculation

A systemic review study in 2016 showed that early feeding has a significantly shorter length of hospital stay (*p*<0.01) compared to the late timing of feeding with a difference of −1.72 days and not associated with an increase in clinically relevant complications [26]. Several other studies also support early nutrition for surgery patients significantly shortening the length of hospital stay [27–29].

LOS was chosen to calculate the sample size because it has been used widely as a primary outcome in most nutrition-related RCT studies [30–32] among patients undergoing surgery. The sample size was calculated based on the data from a study conducted on colorectal cancer patients undergoing surgery [30]. The primary outcome was calculated based on the difference in LOS between two groups (control and intervention group) which was 3.45 days.

A large effect size of 0.8 for clinical significance was assumed, and practicality for this research was considered, with a power (*β*) of 90% and a probability (*α*) of 0.05. Allowing for a “drop-out” rate of 20% for the RCT study, we aim to recruit participants who will be included in each group, with the final sample size calculated as 68 participants with 34 participants in each group, respectively.

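### Operation class is neither a randomisation stratum nor a named covariate for length of stay, although entry covers a broad range of major operations

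*Protocol article*

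**What the plan says.** **Entry.** Study population states: "The inclusion criteria are those who are receiving elective major surgery treatments for gastrointestinal and oncology-related surgery, aged from 18 to 65 years old". The exclusions remove "elective major surgery treatments other than gastrointestinal and oncology-related including bariatric surgery" and "those who require emergency surgery". No organ site or procedure is listed.

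**Planning.** Sample size calculation states: "The sample size was calculated based on the data from a study conducted on colorectal cancer patients undergoing surgery". The figure taken is the "difference in LOS between two groups (control and intervention group) which was 3.45 days". The standardised effect of 0.8 that enters the calculation is described as an assumption, chosen partly on practical grounds. No SD is given. The result is 34 per group, 68 in all, with 20% allowed for dropout.

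**Randomisation.** The section of that name states: "The randomization with body mass index (BMI) and gender stratification will be conducted to assign participants". Blocks are of four. Operation class is not a factor.

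**Analysis.** Analysis of results compares the groups by ANOVA, or by rank tests if the data are not normal, without covariates. It then mentions ANCOVA or logistic regression, adjusted for potential confounders that it does not name, as a way to find predictors of length of stay. Disease type appears there only as a baseline descriptor.

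**Status.** Trial status reports that recruitment was completed on 31 December 2021.

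**The concern.** Length of stay after surgery is the primary outcome, and the kind of operation plausibly influences it. If mean stay differs between the admitted classes, that difference adds to the variance of an unadjusted comparison. The design does not balance class between arms, and the stated group comparison does not remove its effect. With 34 per arm, both the loss of power and the size of a chance imbalance could matter. The planning figures contain no visible allowance for this: the only length-of-stay difference used for the sample size comes from a narrower population than the one admitted.

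**Working it through.** **Step 1: reproduce the plan's figure.** Inputs from Sample size calculation: d = 0.8, power 90%, alpha 0.05 (sidedness not stated), dropout 20%.

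Normal approximation: n per arm = 2(z_alpha + z_beta)² / d².
- Two-sided: 2(1.960 + 1.282)² / 0.64 = 32.8, so 33. The t-test version gives 33.8, so 34, which is 68 in all **before** dropout.
- One-sided: 2(1.645 + 1.282)² / 0.64 = 26.8, so 27. Then 27/0.8 = 33.75, so 34 per arm and 68 **after** dropout.

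The stated 68 is therefore reproduced in two ways. Two-sided power at d = 0.8 is 90% with 34 analysed per arm and 82% with 27. Both bases are carried forward, because 34 less 20% is about 27.

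**Step 2: implied SD.** If 3.45 days and 0.8 belong together, SD = 3.45/0.8 = 4.31 days. This is an inference, since the article states no SD.

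**Step 3: add a difference between operation classes.** Assumptions, none of them from the documents: two equally common classes, within-class SD 4.31 days, mean stays differing by a gap g, and the same treatment difference of 3.45 days in both classes. The between-class variance is g² × 0.5 × 0.5, so

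total SD = √(4.3125² + g²/4), and d = 3.45 / total SD.

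| Assumed gap (days) | Total SD (days) | d | Power, 34 per arm | Power, 27 per arm |
|---|---|---|---|---|
| 0 | 4.31 | 0.80 | 90% | 82% |
| 3 | 4.57 | 0.76 | 87% | 78% |
| 5 | 4.98 | 0.69 | 80% | 70% |
| 8 | 5.88 | 0.59 | 66% | 56% |

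Power is for the two-sided 5% t-test.

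**Step 4: chance imbalance.** Suppose 34 of 68 patients are in one class and class is ignored in allocation. The exact hypergeometric probability that the arms differ by 15 percentage points or more in that class is about 23%. A 15-point difference with a 5-day gap moves an unadjusted estimate by 0.15 × 5 = 0.75 day. This is one way in which the variance in Step 3 shows itself, and is not to be added to it.

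**Step 5: what adjustment recovers.** Under the Step 3 model, a class term brings the residual SD back to 4.31 days. Power then returns to close to the top row of the table, less the small cost of one or two degrees of freedom.

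**The case against.** **The plan already allows adjustment.** Analysis of results does provide for ANCOVA with confounders in relation to length of stay, disease type and treatment are recorded, and an analysis plan not shown may list the covariates. A reader might infer that operation type is left wholly uncontrolled, and the text does not support that. What stands is narrower. The stated group comparison is unadjusted, the ANCOVA is framed as a search for predictors, and operation class is not named.

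**The magnitude is hypothetical.** This is true. The gaps and the equal split are assumptions, and at a 3-day gap the loss is only about 3 to 4 points of power. The planning study may also contain some mix of operations, because colorectal cancer surgery is not one procedure. If so, part of the between-class variance is already in the 4.31 days and the table overstates the loss.

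**The planning effect is not purely colorectal.** Also true. The 3.45 days come from that population, but the 0.8 that drives the sample size is an assumed value.

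**Broad entry suits a pragmatic trial.** Accepted. The point is not that entry should be narrower, and it is not unlimited.

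**Stronger readings that fail.** One might infer a biased comparison, but randomisation rules out systematic bias by operation class, and chance imbalance is random error that the confidence interval already carries. One might also see a contradiction between the entry criteria and the abstract's "Perioperative malnutrition is common in patients undergoing gastrointestinal-oncology surgery". That is a general background sentence and does not define the trial population. The objective, design and entry sections use matching wording.

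**Conclusion.** The point holds as one of precision. Operation class is not balanced by design and is not named as a covariate in the primary comparison, although the admitted operations are wider than the colorectal cancer surgery that supplied the 3.45 days. Under the stated assumptions, two-sided power falls from 90% to between 87% and 66% at 34 per arm, or from 82% to between 78% and 56% at 27 per arm, for gaps of 3 to 8 days. These figures rest on the inferred SD of 4.31 days applying within class, two equally common classes and a common treatment effect. The documents cannot say where in the range this trial lies. The loss is avoidable at almost no cost, which is the reason to act.

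**What to change.** Before analysis, define the primary length-of-stay comparison as an ANCOVA, on log length of stay if the data are skewed, with treatment group and planned operation class as fixed terms. Classes could be, for example, colorectal, upper gastrointestinal or hepatobiliary, and other. Assign class from the operation planned before allocation, not the one performed, so that it is a true baseline covariate. The unadjusted comparison can be kept as a supporting analysis.

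The cost is 1 to 2 degrees of freedom and assigning each participant to a class, with no extra patients or procedures. On the log scale the effect is a ratio of stays, so the power figures above, which are in days, would not carry over directly. Adding operation class as a stratum is no longer possible, because recruitment is complete.

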### Recruitment

Potential patients who are attending the surgical clinic will be approached by the project team member. They will inform all potential participants of the study procedures. However, the study is single-blinded when the investigator but not the study participants knows which treatment has been allocated. The patient information sheet and consent form will be given to the eligible subjects who have agreed to be recruited for the study. Subjects will be allowed to bring back the consent form if they are keen to seek advice from their family member. The consented participants will be randomized into one of the two groups; either into intervention (SS) or control (NN) group.

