#### Intervention group, Group SS

Group SS will be receiving tailored, more intensive, and ongoing nutrition support and lifestyle advice as compared to Group NN. They will be supplemented with oral nutrition support (ONS), available in 400g/can, providing 226 kcal/serving and 9.6 g protein/serving. ONS will be prescribed according to the patient’s requirement, from 1 to 4 servings a day*.* ONS consumption should be daily from 7 to 14 days until 6 h before the scheduled surgery. Patients are encouraged to consume ONS in a small portion, frequently and in between meals. They also will receive intensive and detailed nutrition counseling at each visit. Nutrition counseling consists of adequate energy and protein according to requirement, fluid and salt intake, replenishment of micronutrients, and controlling blood glucose levels before surgery. Follow-up phone calls will be done from time to time to monitor their progress.

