#### Control group, Group NN

Participants in Group NN which is referred to as the control group will receive the standard care of the clinic without getting supplemented with ONS. Nutritional advice will be based on a guideline specifically focused on the treatment of symptoms such as nausea, vomiting, loss of appetite, and diarrhea, and how to deal with the symptoms through nutritional approaches. The advice will be given by clinicians or nurses in the clinic. Those who are identified as having moderate and severe malnutrition will be referred to a dietitian for nutrition counseling. Participants in this group will also have to follow up through phone calls from time to time to assess and monitor their nutritional status before a scheduled surgery. The researcher will attend to any problems faced by participants in this study.

All participants will receive standard postoperative care from clinical and nurse staff with the commencement of free fluids and reintroduction of the normal diet without interference from the researcher or protocol. ONS will be given after surgery, only to the intervention group (Group SS) starting on the first day of nourishing fluid/diet allowance until the day of hospital discharge according to the prescription given. On the other hand, participants in the Group NN would not be given any ONS at postoperatively (Table 2).

**Table 2 Tab2:** ONS allocation

Group	Preoperation	Postoperation
Group 1 (SS)	Supplements	Supplements
Group 2 (NN)	No supplements	No supplements

All participants will have to follow up either at an outpatient clinic or home visit 4 weeks after hospital discharge. Regular (fortnightly) contact with all participants will be maintained for 4 weeks after discharge to monitor their nutritional status and progress. Control groups will be treated exactly as the intervention group apart from the ONS provided.

Participants also will be monitored for complications throughout the study period. Monitoring will occur by daily observation of the participant, checking their medical and nursing notes, and liaising with the attending surgical team and nursing staff. At the same time, complications will be noted as major or minor by using a validated criterion [23].

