### Secondary outcome measures

#### Nutritional status

##### The scored Patient-Generated Subjective Global Assessment (PG-SGA©)

The scored PG-SGA© consists of two sections with seven domains. The first section, which will be completed by the participant, is in the form of a checklist and comprised weight, food intake, symptoms, activities, and function. The second section will be completed by the researcher as it covers the disease and its relation to nutritional requirements, and determination of metabolic demands, and will be followed by a nutrition-related physical examination, including subjective body composition (i.e., fat, muscle, and fluid status).

A score ranging from 0 to 4 will be given for each domain depending on the impact on the nutritional status. PG-SGA© scores that range from 0 to 35 reflect a greater risk of malnutrition or indicate a lower nutritional status of the patient. These scores will be transformed into global ratings—Stage A, Stage B, and Stage C—which will represent the states of being well-nourished, moderately malnourished, and severely malnourished, respectively. Then, the criticality of the need for nutritional intervention will be identified and classified based on the scores with 0 to 1 point for those requiring no intervention, health education for 2 to 3 points, dietetic intervention for 4 to 8 points, and nutrition support for ≥9 points.

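### The trial is called single-blinded with participants as the blind party, but its own open comparison of ONS with no ONS leaves neither participant nor investigator blind

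*Protocol article*

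**What the plan says.** The Design section states: "This study will be a single-blinded, pragmatic randomized clinical trial with two arms comparing an intervention group with a control group". The Recruitment section defines the blinding: "the study is single-blinded when the investigator but not the study participants knows which treatment has been allocated".

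The treatment sections describe a visible difference between the arms. For Group SS: "They will be supplemented with oral nutrition support (ONS), available in 400g/can, providing 226 kcal/serving and 9.6 g protein/serving". Group NN "will receive the standard care of the clinic without getting supplemented with ONS", and after surgery "participants in the Group NN would not be given any ONS at postoperatively". Table 2 shows supplements in both periods for SS and in neither for NN. The Control group section adds: "Control groups will be treated exactly as the intervention group apart from the ONS provided". Under Data collection procedure, SS participants keep the ONS packaging, which the researcher collects at visit 1 and at discharge. Under Recruitment, all potential participants are told the study procedures.

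On assessment, the first section of the PG-SGA is filled in by the participant, and for the rest "The second section will be completed by the researcher". The investigators take the anthropometric measurements. On allocation, the Randomization section says: "The randomization will be based on a block method for a block size of four", stratified by BMI and gender, through an online platform.

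**The concern.** A single-blind label tells the reader that one party's expectations have been kept out of the results. Here that party is the participant. The participant cannot be unaware of being handed a supplement to take daily, or of receiving none after hearing what the study involves.

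Several outcomes depend on what the participant reports or how hard the participant tries: dietary records, the first PG-SGA section and handgrip. Others depend on a rater who, by the article's own definition, may know the arm: the second PG-SGA section, mid-arm circumference and triceps skinfold. Readers who take the label at face value would credit these outcomes with a safeguard that was not in place.

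A smaller question follows from open delivery. Past allocations can be seen from who receives ONS, so a single small block size could let someone who tracks them anticipate later ones.

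**Working it through.** **Blinding: the statements side by side**

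| Party | Claimed status | What the article describes |
|---|---|---|
| Participant | Blind (Recruitment) | SS takes ONS and keeps the packaging; NN gets none; no placebo or sham; procedures explained to all potential participants |
| Investigator | Not blind (Recruitment) | Scores PG-SGA section two (as the researcher), takes anthropometry, collects packaging |

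Parties named: 2. Parties that can be blind on this description: 0. No other party, such as an independent assessor, is stated to be blind.

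**Block size: a conditional calculation**

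Inputs from the article: block size 4 with two As and two Bs; six arrangements (Randomization); 68 participants (Sample size calculation). Assumptions that are not in the article: the recruiter knows the block size, sees every past allocation within each stratum, and guesses the arm with more places left.

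1. Arrangements: C(4,2) = 6, which agrees with the article.
2. Determined positions over the 6 × 4 = 24 places: the fourth place always (6), and the third when the first two match (AABB and BBAA, so 2). Total 8/24 = 33.3%.
3. Expected correct guesses per block: 1/2 + 2/3 + 2/3 + 1 = 17/6. Divided by 4 this is 17/24 = 70.8%, against 50% by chance.
4. Allowing for incomplete blocks: the number of BMI categories is not given, so 2, 3 or 4 categories by two genders were assumed, giving 4, 6 or 8 strata. Patients were assigned to strata at random with equal probability (simulation of 68 patients, 3,000 repetitions).

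| Strata (assumed) | Determined | Patients of 68 | Guessed correctly |
|---|---|---|---|
| Full blocks | 33.3% | 22.7 | 70.8% |
| 4 | 30.9% | 21.0 | 69.7% |
| 6 | 29.7% | 20.2 | 69.2% |
| 8 | 28.4% | 19.3 | 68.6% |

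Stratification lowers predictability only slightly. Even under these assumptions, about 67% to 72% of allocations are not known with certainty.

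**The case against.** The best defence of the trial is that the label matters little for its main result. Length of stay is a count of days from postoperative day 1 to discharge, not a rating. Albumin, white count and haemoglobin come from the medical report, and C-reactive protein from stored serum. Randomisation through an online platform remains in place. All of this stands, and it limits the harm mainly to the reported, rated and effort-dependent secondary outcomes. It does not make the blinding statement true.

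One could also suppose that participants were kept unaware of what the other arm received. The article describes no such arrangement, and it says that the study procedures are explained to all potential participants.

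A reader might go further and infer three things that the text does not support:

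- **That the unblinded investigator recruits with knowledge of the block size.** The article says that a project team member approaches patients. It does not say that this person is the unblinded investigator, sees past allocations or knew the block size. The size appears in an article that already reports recruitment as complete.
- **That the researcher influences discharge.** The contact with the surgical and nursing staff described under the Control group heading is for monitoring complications. The same section says that the researcher does not interfere with the return to fluids and normal diet.
- **That an unblinded researcher measures handgrip.** The Handgrip strength section names no assessor. The concern there is the participant's own effort.

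**Conclusion.** The single-blind label is wrong as written. It contradicts the article's own description of treatment, and neither named party is blind. This rests on the text alone and needs no outside figure. It should be corrected because it affects how the secondary outcomes are read, but it does not invalidate the trial.

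Predictability of allocation is secondary and conditional: about 28% to 33% of allocations determined and about 69% to 71% guessable, only if recruiters knew the block size and tracked allocations by stratum. It would be an overstatement to say that protection against bias is absent. Randomisation and the online platform remain, and the article does not show that anyone exploited, or could exploit, the block structure.

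**What to change.** 1. Replace single-blinded with open-label under Design and Recruitment, and state who, if anyone, is blinded.
2. State that length of stay is taken from admission-record dates of surgery and discharge held by the hospital.
3. Label self-recorded intake, PG-SGA (section two scored by the researcher), anthropometry and handgrip as unblinded assessments, open to expectation bias when results are interpreted.
4. The Trial status section gives 31 December 2021 as the end of recruitment, so the block size can no longer be changed. Report the single block of four as a limitation and give a descriptive baseline comparison by arm. Apparent balance in 68 participants would be reassuring but would not rule out selection.

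The cost is wording and reporting only, with no extra assessor or data. The downside is a less favourable design label.
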